### Recruitment

Participants will be recruited at two specialized treatment centers in the Netherlands: Mondriaan/PsyQ Academic Anxiety Center and Altrecht Academic Anxiety center. Clinicians refer patients who potentially meet inclusion criteria after a standard intake procedure. Potential participants are invited for an information session with the research assistant, who examines inclusion and exclusion criteria. After providing informed consent, baseline assessments (T1) will be made. Afterwards, participants are randomized to one of conditions (EMDR therapy + exposure therapy or supportive counseling + exposure therapy). Inclusion will continue until 50 panic disorder patients completed posttreatment (T3).

### Participants

Patients will be eligible to participate in the study if they meet the following criteria: (1) at least 18 years of age; (2) sufficient mastery of Dutch language and able to complete questionnaires and understand informed consent information; (3) meet DSM-5 criteria for (primary) panic disorder (with or without agoraphobia); (4) stable medication for at least six weeks and willingness to keep medication stable during the study period (until FU1); and (5) self-reported ability to refrain from alcohol or drugs 24 h before and after each session. General use of alcohol or drugs will be discouraged. Use of sedating medication (e.g., benzodiazepines) is not a contra-indication, but participants are discouraged to use sedating medication before or after treatment sessions and subsequent days. Use of sedating medication will be registered. Patients will not be eligible if they meet any of the following exclusion criteria: (1) self-reported neurological disorder; (2) acute or recent history of suicide attempts according to the Mini-International Neuropsychiatric Interview (M.I.N.I.) section C; (3) self-reported visual or auditory impairments that could hinder treatment; (4) self-reported epilepsy, pregnancy, or heart disease (only for fear-conditioning task); (5) self-reported current psychological treatment for other DSM-5 disorder; and (6) not willing or able to fill in (online) questionnaires.

### Randomization

After baseline measures (T1) participants are randomized to one of the two conditions by a research assistant who does not conduct assessments, using computerized randomization (REDCAP) [53, 54]. Stratified randomization will be used to reduce bias by treatment center [55], to guarantee a balanced distribution of participants across conditions.

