### Sample size

For the primary objectives of efficacy, tolerability, and adherence, the sample size was calculated using G*power 3.1 [56] using a 2 (groups) × 2 (time) repeated-measures ANOVA. Given the active control condition, we expect a medium effect size [9]. For a between group effect size of f = 0.25, alpha 0.05, power 0.80, 0.5 correlation among repeated measures and 1.0 non-sphericity correction, a total sample size of 98 participants is needed for two-sided testing. Although no formal method is available to determine a repeated-measures ANOVA sample size using Bayesian statistics, approximations for t-test are available [57]. For a one-sided *t*-test with a power of 0.80 and a Bayes factor of 3 (indicating evidence for the data coming from the alternative than the null hypothesis), 87 participants are needed and for a Bayes factor of 5, 99 participants are needed. Originally, we aimed to recruit 100 participants (see pre-registration: ISRCTN - ISRCTN29668369). However, the COVID-19 pandemic has seriously impacted the number of referrals of patients with panic disorder. To increase the feasibility of the study, we formulated directional hypotheses and decided to use one-sided testing, which reduces our sample size to 50 participants [58]. This change was approved by the ethical committee on February 8 2023. Participants who will not show up to therapy sessions in the first two weeks of treatment will be considered non-compliant and will be described as dropouts. Dropouts will not be excluded from intent to treat analyses, but will be replaced by additional participants to preserve statistical power. The completer sample size will be sufficient to address secondary objectives.

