### Data analysis

Data of all randomized participants will be analyzed on intent-to-treat basis as well as the completer sample. The primary outcomes (panic disorder symptomology) as well as secondary outcomes (tolerability and adherence) will be analyzed using a mixed regression model, using baseline scores as a covariate. This enables us to identify any fixed or random effects resulting from the treatments and changes over time. To analyze count date (e.g., drop-out, no show), Poisson or negative binomial regression will be used. Data analysis strategies for the secondary goals (goals 2–4) will be pre-registered in prior to analysis in Open Science Framework [52].

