### Protocol version

Version 1: original, issue date 26–08-2020. Version 2: amendment adding treatment integrity (video recordings), issue date 26–05-2021. Version 3: amendment changing information letter and adding time stamps in questionnaire response, issue date 27–07-2021. Version 4: amendment to 1) reduce the sample size for panic disorder from *N* = 100 to *N*= 50 to enhance feasibility of the study and adapting statistical analyses accordingly (one-sides testing instead of two sided testing), 2) terminate a RCT in social anxiety disorder, due to a low influx of participants, 3) the option for participants not to consent with audio and video recordings, 4) change the session frequency (once instead of twice weekly), 5) stopping the Experience Sampling Measurements, 6) enable videoconferencing aside from the pandemic restrictions, 7) report the study progress, issue date 08-02-2023.

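### Randomisation is stratified by treatment centre, but the stated goal 1 model does not name centre; if centre predicts outcome beyond baseline, leaving it out makes the test conservative and costs a little power

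*Protocol article*

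**What the plan says.** All references are to the protocol article.

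- **Recruitment:** "Participants will be recruited at two specialized treatment centers in the Netherlands".
- **Randomization:** "Stratified randomization will be used to reduce bias by treatment center". Centre is the only stratification factor mentioned.
- **Data analysis:** the primary outcomes, and the tolerability and adherence outcomes, "will be analyzed using a mixed regression model, using baseline scores as a covariate". The next sentence adds: "This enables us to identify any fixed or random effects resulting from the treatments and changes over time". Centre is not named as a covariate, a fixed effect or a random effect. The section leaves the strategies for goals 2 to 4 to later pre-registration and makes no such reservation for goal 1.
- **Sample size:** the calculation was done "using a 2 (groups) × 2 (time) repeated-measures ANOVA", with these inputs: "For a between group effect size of f = 0.25, alpha 0.05, power 0.80, 0.5 correlation among repeated measures and 1.0 non-sphericity correction". It gives 98 participants for two-sided testing, reduced to 50 with one-sided testing.

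**The concern.** Stratifying by centre forces the arms to be nearly balanced within each site. Any difference in outcome between the sites then largely cancels out of the treatment comparison, so the treatment estimate really is more precise. A model without centre does not recognise this. It leaves the between-centre variance in the residual and reports a standard error larger than the true one. The test then rejects less often than its nominal level under the null, and it has less power than the design could deliver.

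What is at stake is efficiency. The stated model does not use a factor that the design already balances on, in a trial with little precision to spare.

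**Working it through.** **1. The plan's own figure.** The between-group test in a repeated-measures ANOVA with m = 2 measurements has noncentrality λ = f²·N·m / (1 + (m − 1)ρ), with 1 and N − 2 degrees of freedom. With f = 0.25, ρ = 0.5 and two-sided alpha 0.05, the smallest even N with power 0.80 is 98, as stated. With the same inputs and one-sided alpha 0.05, the required N is 76, and N = 50 gives power 0.643. The shortfall at 50 is a separate sample-size matter. Here 0.643 serves only as the starting power.

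**2. Noncentrality at N = 50.** λ = 0.0625 × 50 × 2 / 1.5 = 4.167, and √4.167 = 2.041. A baseline-adjusted comparison gives the same value. The standardised difference is 2f = 0.5, the residual variance is 1 − 0.5² = 0.75, the standard error is √(0.75 × 4/50) = 0.245, and 0.5/0.245 = 2.041. The planning figure therefore carries over to the model with the T1 score as covariate.

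**3. Adding a centre effect.** Let R² be the share of post-baseline residual variance that centre explains. The documents give no value for it, so every R² above 0 is an assumption. Allocation is taken as 1:1, since no ratio is stated.

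- True noncentrality under stratified allocation: 2.041 / √(1 − R²), which is 2.094 at 5% and 2.152 at 10%.
- Model with centre: reject above t(0.95; 47), and take power from the noncentral t.
- Model without centre: the standard error is too wide by the factor 1/√(1 − R²). On the true scale this amounts to rejecting above t(0.95; 48)/√(1 − R²) = 1.677/√(1 − R²).
- Size without centre: P(t48 > 1.677/√(1 − R²)). At 5% the cut-off is 1.721 and at 10% it is 1.768.

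| Assumed R² | SE too wide by | One-sided size, no centre | Power, no centre | Power, with centre | Gain (points) |
|---|---|---|---|---|---|
| 0% | 0% | 0.050 | 0.643 | 0.643 | 0 |
| 2% | 1.0% | 0.048 | 0.645 | 0.651 | 0.6 |
| 5% | 2.6% | 0.046 | 0.647 | 0.662 | 1.6 |
| 10% | 5.4% | 0.042 | 0.651 | 0.683 | 3.2 |
| 20% | 11.8% | 0.033 | 0.659 | 0.727 | 6.8 |

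Gains are taken from unrounded powers.

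**4. Simulation check.** There were 8,000 runs per setting, with N = 50, permuted blocks of 4 within centre, and a baseline-adjusted linear model with and without centre.

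- *Sites split 25/25:* at 5% the ratio of standard errors was 1.026, size without centre 0.046, and power 0.635 without and 0.650 with centre. At 10% the figures were 1.055, 0.041, 0.630 and 0.664. At 0% there was no gain (0.640 and 0.639).
- *Sites split 35/15:* at 10% the ratio was 1.055, and power 0.647 and 0.677.

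The Monte Carlo error of a single power figure is about √(0.65 × 0.35/8000) = 0.005, so simulation and formula agree.

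These figures concern the continuous outcomes under a linear model. The count outcomes (drop-out, no-show) were not calculated.

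**The case against.** The strongest objection is that the Data analysis section is one paragraph in a journal article. It does not say that the baseline score is the sole adjustment and does not exclude a centre term. A full protocol or analysis plan, not shown, may contain one. That stands as a limit: the claim can only be that the stated model does not name centre. The point is still worth raising because the section itself specifies the covariate for the goal 1 model, omits the one factor used in stratification, and defers only goals 2 to 4.

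Four stronger readings might be inferred and are not supported:

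- **That precision is certainly being lost.** This needs a centre effect beyond baseline. None is documented, and at 0% there is no loss. Where the sites differ mainly in initial severity, the T1 score already captures much of the difference.
- **That the error bars are invalid without centre.** The error is conservative: the true size is at or below 0.05, so false positives do not increase. Adding centre is a matter of efficiency.
- **That the gain is 1.9 or 4.0 points.** Those figures compare 0.662 and 0.683 with 0.643, the power when centre explains nothing. At the same centre share the gains are 1.6 and 3.2 points.
- **That the protocol amendment needs a model term for the same reason.** The Protocol version section lists a step to "change the session frequency (once instead of twice weekly". Randomisation was not stratified by protocol version, so the argument about too-wide standard errors does not carry over. The number of participants treated under each schedule is not given, so no size can be attached to it.

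**Conclusion.** The point holds as a modest, conditional one. The design stratifies by centre and the stated goal 1 model does not name it. If centre explains 5% to 10% of the residual variance, leaving it out costs 1.6 to 3.2 points of power and lowers the one-sided size to between 0.046 and 0.042. If centre explains nothing beyond baseline, the cost is nil. These figures rest on N = 50, 1:1 allocation, the planning effect (f = 0.25, ρ = 0.5), one-sided 0.05 and an assumed centre share. A centre term recovers a few points at most. It does not repair the gap between power of 0.643 and the intended 0.80, and the point should not borrow weight from that gap.

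**What to change.** Add one sentence to the Data analysis section: the goal 1 models include treatment centre as a fixed effect besides the T1 score. With two centres this costs one degree of freedom, and at N = 50 power is essentially unchanged even if centre has no effect (0.643 either way). If the full analysis plan already has the term, the article need only say so. The wording should be settled before the data are analysed. No change to randomisation, data collection or sample size is involved.

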### Sample size

For the primary objectives of efficacy, tolerability, and adherence, the sample size was calculated using G*power 3.1 [56] using a 2 (groups) × 2 (time) repeated-measures ANOVA. Given the active control condition, we expect a medium effect size [9]. For a between group effect size of f = 0.25, alpha 0.05, power 0.80, 0.5 correlation among repeated measures and 1.0 non-sphericity correction, a total sample size of 98 participants is needed for two-sided testing. Although no formal method is available to determine a repeated-measures ANOVA sample size using Bayesian statistics, approximations for t-test are available [57]. For a one-sided *t*-test with a power of 0.80 and a Bayes factor of 3 (indicating evidence for the data coming from the alternative than the null hypothesis), 87 participants are needed and for a Bayes factor of 5, 99 participants are needed. Originally, we aimed to recruit 100 participants (see pre-registration: ISRCTN - ISRCTN29668369). However, the COVID-19 pandemic has seriously impacted the number of referrals of patients with panic disorder. To increase the feasibility of the study, we formulated directional hypotheses and decided to use one-sided testing, which reduces our sample size to 50 participants [58]. This change was approved by the ethical committee on February 8 2023. Participants who will not show up to therapy sessions in the first two weeks of treatment will be considered non-compliant and will be described as dropouts. Dropouts will not be excluded from intent to treat analyses, but will be replaced by additional participants to preserve statistical power. The completer sample size will be sufficient to address secondary objectives.

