## Background

Anxiety disorders are among the most common mental disorders, with about one out of 14 people meeting diagnostic criteria at any point of time [1]. These disorders comprise panic disorder, agoraphobia, social anxiety disorder, specific phobia, and generalized anxiety disorder. Their key elements are excessive fear in anticipation or the presence of the feared (innocuous) stimulus/stimuli and avoidance of disorder-related situations [2], which cause personal suffering and/or functional impairment [3]. Annual societal costs associated with anxiety-related disorders are estimated at about €74 billion in the European Union [4] and $42 billion in the United States [5].

Cognitive-behavioral therapy (CBT) is the psychological treatment of choice for anxiety disorders recommended in clinical guidelines [e.g., [6]], and it typically includes a combination of cognitive restructuring and behavioral (e.g., exposure) interventions [6, 7]. During exposure therapy, patients are systematically confronted with stimuli and situations associated with their anxiety disorder (e.g., bodily sensations in case of panic disorder), so that the patient learns that the anticipated feared outcome does not occur (e.g., having a heart attack) [8]. Meta-analyses have shown large effect sizes for CBT in anxiety disorders, especially when exposure strategies are used [9, 10].

A recent meta-analysis, however, shows that exposure-based CBT is moderately efficacious for anxiety disorders compared to other interventions when controlling for non-specific treatment or placebo (pill or psychological) effects [9]. There is substantial room for improvement for at least four reasons. First, about 25–30% of patients refuse to start exposure therapy, because they find it too aversive [11, 12]. Second, about 10–20% of patients drop out prematurely [12–14]. Third, although meta-analyses show substantial effect sizes for (exposure-based) CBT, the response rate (i.e., the percentage of patients showing significant clinical improvement) is around 50% [15]. Finally, little research has focused on relapse after (exposure-based) CBT [16–18], but recent findings suggest that it occurs in about 14% of cases [17]. Additionally, laboratory research has shown that even when exposure-based training is initially successful, learned fear can later return [19]. Taken together, these results underline the need for treatment optimization.

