## Goals of the current study:

The main goal of this multicenter Randomized Controlled Trial is to investigate whether EMDR therapy with exposure therapy, relative to supportive counseling with exposure therapy, improves treatment efficacy, tolerability, and adherence in patients with panic disorder. The primary outcome measures are panic-related symptoms. Secondary outcome measures are: tolerability of exposure therapy (initial avoidance, willingness to start exposure therapy, considered drop-out; no-show and drop-out), related symptomatology (generalized anxiety, depression) and functional impairment. We hypothesize that: (1) EMDR therapy will be more effective in reducing panic-related symptoms, compared to supportive counselling from baseline (T1) to between-treatments (T2). (2) EMDR therapy + exposure therapy will be more effective in reducing panic-related symptoms, compared to supportive counseling + exposure therapy at post-treatment (T3). (3) EMDR therapy will result in higher tolerability of exposure therapy (less initial avoidance, more willingness to start exposure therapy, less considered drop-out; less no-show and actual drop-out) compared to supportive counseling. We further hypothesize that: (4) EMDR therapy will be more effective in reducing related symptomatology (generalized anxiety, depression) and functional impairment, compared to supportive counseling from baseline (T1) to between-treatments (T2). And (5) EMDR therapy + exposure therapy will be more effective in reducing related symptomatology (generalized anxiety, depression) and personal suffering/functional impairment, compared to supportive counseling + exposure therapy at post-treatment (T3).

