**Fig. 2 Fig2:**
[figure not shown]
Design flowchart; T1-3: measurements, FU1-2: follow up measurements. EMDR: EMDR therapy, SC: supportive counselling

After baseline measurements (T1), participants will be randomly allocated to one of two conditions: (1) four weekly EMDR therapy sessions followed by eight exposure therapy sessions or (2) four weekly supportive counseling sessions followed by eight exposure therapy sessions. Total study duration is 16 weeks (week 1: baseline measurement T1, week 2: case conceptualization, week 3–6: treatment phase 1; EMDR therapy or supportive counseling, week 7: between-treatments measurement T2, week 8–15: treatment phase 2; exposure therapy, week 16: post-treatment measurement T3). Follow up 1 measurement (FU1) and follow up 2 measurement (FU2) will be conducted one month and six months post-treatment measurement (T3). At FU1, the clinician and participant will determine whether additional treatment is needed. Measurement are conducted by a research assistant blind to treatment allocation. The research protocol has been approved by the Medical Ethical Committee of University Medical Center Utrecht (NL NL73918.041).

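### The f = 0.25 used for sizing is not supported by its cited source for the post-treatment contrast, and at N = 50 one-sided it gives about 64% power, not 80%

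*Protocol article*

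**What the plan says.** All of this is in the protocol article.

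- **Sample size, effect.** The expected effect is introduced with "Given the active control condition, we expect a medium effect size [9" and set by "For a between group effect size of f = 0.25". No other source is given for it.
- **Sample size, model.** The calculation was done "using a 2 (groups) × 2 (time) repeated-measures ANOVA", with "alpha 0.05, power 0.80, 0.5 correlation among repeated measures and 1.0 non-sphericity correction". The result is 98 participants for two-sided testing. The same section then moves to directional hypotheses with one-sided testing and states that this brings the number to 50.
- **Background, on reference [9].** The meta-analysis is reported as showing that "exposure-based CBT is moderately efficacious for anxiety disorders compared to other interventions when controlling for non-specific treatment or placebo (pill or psychological) effects".
- **Study design and general procedure.** The control arm receives "four weekly supportive counseling sessions followed by eight exposure therapy sessions". The EMDR arm receives the same exposure course after its four EMDR sessions.
- **Goals of the current study.** Hypothesis 2 compares the two full packages on panic-related symptoms at T3, after that shared course.
- **Background, last paragraph.** No earlier study is said to have tested whether modulating flashforwards reduces anxiety symptoms by itself or improves exposure-based therapy.
- **Discussion.** The sample size is described as giving enough power for the primary and secondary aims.

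**The concern.** The treatment that [9] evaluated, as the article describes it, is common to both arms. It cannot produce the randomized difference at T3, which is the increment of EMDR over supportive counseling when both are followed by exposure. The document says this increment has not been studied, yet a literature citation stands behind the value used to plan for it. A reader would take f = 0.25 as evidence-based for hypothesis 2 when it is a working assumption.

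The second issue is that the 80% power belongs to 98 participants tested two-sided. The article carries the claim of adequate power forward to 50 participants without giving the power at that size. If the trial ends with a non-significant T3 result, a reader relying on the Discussion could give it more weight as evidence against an added benefit than a trial of this size can bear.

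**Working it through.** **Inputs.** From Sample size: f = 0.25, alpha 0.05, power 0.80, m = 2 repeated measures, correlation ρ = 0.5, sphericity correction 1.0, N = 98 two-sided and N = 50 one-sided. The Randomization section aims for balance but states no ratio, so equal arms (25 each at N = 50) are assumed. For two equal groups d = 2f, so f = 0.25 is d = 0.5.

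**Formula.** For the between-groups factor in repeated-measures ANOVA, the noncentrality is λ = f² × N × m / (1 + (m − 1)ρ), with 1 and N − 2 degrees of freedom. With m = 2 and ρ = 0.5 this is λ = f² × N × 2 / 1.5. One-sided testing at 0.05 corresponds to the F test at 0.10, apart from a negligible chance of rejecting in the wrong direction.

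**Step 1: reproduce the plan's figure.** N = 98, two-sided: λ = 0.0625 × 98 × 2 / 1.5 = 8.17 and power is 0.808. The smallest even N reaching 0.80 is 98. The plan's figure is correct, and this is the model behind it.

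**Step 2: change only the sidedness.** With all other inputs kept, one-sided testing needs N = 76 (λ = 6.33, power 0.802). It does not bring 98 down to 50.

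**Step 3: power at the current size.** N = 50, f = 0.25: λ = 0.0625 × 50 × 2 / 1.5 = 4.17. Power is 0.64 one-sided (0.52 two-sided).

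**Step 4: detectable effect.** At N = 50 one-sided, power reaches 0.80 at f = 0.309 (λ = 0.309² × 50 × 2 / 1.5 = 6.37), that is, f about 0.31 and d about 0.62.

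**Step 5: check against the planned analysis.** Data analysis specifies a mixed regression model with baseline as covariate. A single-time-point comparison adjusted for baseline with correlation 0.5 reduces the variance by the factor 1 − 0.5² = 0.75. With 25 per arm and d = 0.5, the noncentrality is 0.5 × √(25/2) / √0.75 = 2.04, which equals √4.17. Power is again 0.64.

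**Step 6: other models tried.** None gives 50 at f = 0.25:

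| Model | N two-sided | N one-sided |
|---|---|---|
| Between factor, m = 2 | 98 | 76 |
| Between factor, m = 3 | 86 | 68 |
| Group-by-time interaction, m = 2 | 34 | 28 |
| Two-sample t-test, d = 0.5 | 128 | 102 |

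**Step 7: sensitivity at T3.** The documents give no add-on effect, so the lower rows are assumptions (75% and 50% of the planned f), not estimates.

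| f at T3 | Power, N = 98 two-sided | Power, N = 50 one-sided |
|---|---|---|
| 0.25 (planned) | 81% | 64% |
| 0.1875 (assumed) | 56% | 45% |
| 0.125 (assumed) | 29% | 26–27% |

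The range in the last cell is the difference between the exact one-sided t (26.2%) and the F test at 0.10 (26.6%).

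**The case against.** **The citation may only argue for medium rather than large.** The Background contrasts large effects for CBT in general with moderate ones once non-specific effects are controlled. The Sample size sentence can be read as taking that step because the control is active. This is fair, and it means that one cannot say f = 0.25 was lifted from a mismatched contrast. It still accounts only for counseling as an active control, not for the exposure course in the control arm, and it leaves the value an assumption.

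**Wider evidence is mentioned.** Limitations says that effect sizes for EMDR, supportive counseling and CBT are already established. It gives no value there and does not address an increment over exposure.

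**The mismatch is weaker at T2.** EMDR against supportive counseling is a specific therapy against a non-specific psychological control, which is close in structure to what [9] is said to cover, although the therapy differs. This stands, and the point is therefore confined to T3.

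**A reader might infer that the T3 effect must be smaller than medium because exposure is shared.** The documents do not support that. The Background's rationale is that imagery work enhances extinction learning and reduces return of fear, and hypothesis 3 expects exposure to be better tolerated after EMDR. A T3 difference that is preserved or larger is equally compatible with the text.

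**A reader might also infer that hypothesis 2 should become estimation only.** Nothing in the document requires this. With no earlier study of the combination, some assumption was unavoidable, and testing the hypothesis remains legitimate.

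**The 64% is not caused by the source of the effect.** This is correct. It follows from the step to 50 participants and would hold even if f = 0.25 were fully justified. The two parts are related only because both concern what the Sample size section may claim.

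**The interaction model would favour the plan.** At N = 50 and f = 0.25 it gives 93% two-sided or 97% one-sided. But it does not yield the stated 98, so it is not the model the plan used.

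**Conclusion.** The point holds in two limited parts. First, for the T3 contrast f = 0.25 is an unsupported planning assumption: the only source cited concerns, as described, the treatment that both arms share, and the article says the add-on effect is untested. Second, the power is not delivered at the current size. It is about 64% at N = 50 one-sided under the plan's own inputs, about 16 percentage points below 80%, and the detectable effect is f of about 0.31 (d about 0.62).

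This rests on equal allocation, on the between-factor model that reproduces 98, and on the article's own description of [9], which was not at hand. Nor was the source cited for the reduction to 50. If that source supports a different calculation, the article does not show it, and one-sidedness alone does not lead to 50. The powers at f = 0.1875 and 0.125 show sensitivity only and say nothing about the true effect.

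**What to change.** **Sample size section**
- Call f = 0.25 an assumption and stop presenting [9] as its support for the T3 contrast.
- State that N = 50 one-sided gives about 64% power at f = 0.25, and that 80% power needs f of about 0.31 (d about 0.62).
- Add a short range for smaller T3 effects, marked as assumed: about 45% at f = 0.1875 and 26–27% at f = 0.125.

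**Discussion**
- Replace the sufficient-power statement with these figures.
- Add that a non-significant T3 result does not by itself show that EMDR adds no benefit to exposure.

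Hypothesis 2 remains a tested hypothesis. The cost is rewording two paragraphs and stating a less favourable power. Enrolment, visits and data collection do not change.

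### The sample size is computed for a group effect averaged over two unnamed occasions, which neither the main hypotheses nor the planned baseline-adjusted analysis tests, so the stated 80% power does not belong to the planned test.

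*Protocol article*

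**What the plan says.** The Sample size section names the method, "using a 2 (groups) × 2 (time) repeated-measures ANOVA", and its inputs: "For a between group effect size of f = 0.25, alpha 0.05, power 0.80", with "0.5 correlation among repeated measures and 1.0 non-sphericity correction". The result is that "a total sample size of 98 participants is needed for two-sided testing". The effect is described in words: "Given the active control condition, we expect a medium effect size". The section does not say which two of the three time points (T1, T2, T3) form the time factor. It then reports that the target was lowered to 50 with one-sided testing.

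The Goals section states two efficacy hypotheses for panic symptoms. Hypothesis 1 compares the arms on improvement "compared to supportive counselling from baseline (T1) to between-treatments (T2"). Hypothesis 2 compares them at T3. The Data analysis section says that the outcomes "will be analyzed using a mixed regression model, using baseline scores as a covariate". The Discussion asserts that the sample size is adequate for the primary and secondary aims.

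**The concern.** A power statement is informative only for the contrast it was computed for. Here three sections describe three different things: a group effect averaged over two occasions (Sample size), a change to T2 and a difference at T3 taken separately (Goals), and a baseline-adjusted comparison (Data analysis). The meaning of f = 0.25, and hence of the word medium, also depends on which occasions are averaged.

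At stake is whether a reader can rely on 80% power for a medium effect. The effect size and correlation printed in this section are the only basis the article gives for judging the adopted target of 50 and the Discussion's claim of adequate power. If they belong to another test, that judgement cannot be made from the article.

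**Working it through.** **Inputs from the Sample size section.** f = 0.25, alpha 0.05 two-sided, power 0.80, m = 2 occasions, r = 0.5, stated N = 98; adopted N = 50, one-sided. **Assumed:** 1:1 allocation (no ratio is printed), equal SD at each visit, and d = 0.5 as the meaning of a medium effect at one visit (d = 2f for two equal groups).

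**1. Reproduce 98.**
- Between-groups main effect: lambda = f² x N x m / (1 + (m - 1)r), on 1 and N - 2 df. At N = 98: 0.0625 x 98 x 2 / 1.5 = 8.17, power 0.808. N = 96 falls just short (0.799). This reproduces 98 exactly.
- Group-by-time interaction: lambda = f² x N x m / (1 - r). The required N is 34. This does not reproduce 98.

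The figure is therefore the group main effect on each patient's mean over two occasions, which also fits the section's description of the effect as between-group.

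**2. What f = 0.25 means.** It is a difference of 0.5 SD in the two-occasion mean.
- If the occasions are T1 and one follow-up: randomisation follows T1, so the expected difference at T1 is zero. Then (0 + d)/2 = 0.5, so d = 1.0 at follow-up.
- If the occasions are T2 and T3: (d_T2 + d_T3)/2 = 0.5, for example d = 0.5 at each.

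The article does not settle which applies.

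**3. The planned type of contrast.** For a baseline-adjusted arm difference at one visit, SE = sqrt((4/N)(1 - r²)) in SD units, on N - 3 df, where r is the correlation between T1 and that visit. With d = 0.5, two-sided alpha 0.05 and 80% power:

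| r | Required N |
|---|---|
| 0.3 | 118 |
| 0.5 | 98 |
| 0.7 | 68 |

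The agreement at r = 0.5 arises because the two variance factors coincide there: (1 + r)/2 = 0.75 and 1 - r² = 0.75. They differ at r = 0.3 and 0.7.

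If hypothesis 1 were instead tested literally as a change score, the variance factor would be 2(1 - r) = 1 at r = 0.5. The required N would be 128, with 69% power at N = 98.

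**4. Power at the adopted target.** N = 50, one-sided alpha 0.05, d = 0.5, 47 df:

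| r | SE | d/SE | Power |
|---|---|---|---|
| 0.3 | sqrt(0.08 x 0.91) = 0.270 | 1.85 | 57% |
| 0.5 | sqrt(0.08 x 0.75) = 0.245 | 2.04 | 64% |
| 0.7 | sqrt(0.08 x 0.51) = 0.202 | 2.48 | 79% |

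The T1-T2 and T1-T3 correlations are not given in the article, so r = 0.3 to 0.7 is an assumed range.

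**The case against.** The strongest reply is that baseline is a covariate in the planned model, which leaves exactly two outcome times, T2 and T3. Read that way, f = 0.25 is d = 0.5 averaged over both, as the authors say, and the printed 0.5 is the T2-T3 correlation. If the model's arm effect were tested jointly over T2 and T3 (d = 0.5 at each, all correlations 0.5), the residual variance would be 0.75 - 0.25 = 0.50. Power at N = 98 would then be 0.93, and 66 participants would suffice. Even for a single visit, 98 gives 81% at the printed correlation. In addition, the article condenses a fuller protocol, and 98 has been superseded by 50.

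Much of this stands. A reader might infer that the trial was sized for an effect of 1.0 SD, or that its power for a medium effect is only 29% with 380 participants needed. Those two figures apply to a main effect that includes T1, and the article never says that T1 is one of the two occasions. For the same reason one cannot conclude that the calculation gets the role of the correlation backwards: for T2 and T3, a higher correlation between them rightly raises N. Nor is 98 shown to be wrong.

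What does not stand is that the T2/T3 reading makes the paragraph fit the plan. It still averages two visits that hypotheses 1 and 2 keep apart, and the printed ANOVA makes no baseline adjustment. The mismatch is between statements printed in the article, not a detail left to a longer document. That 98 has been superseded does not help either, because no other calculation for the planned contrast supports 50.

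**Conclusion.** The point holds as a mismatch between the Sample size section, the Goals and the Data analysis. The 98 comes from a group main effect averaged over two unnamed occasions, so the 80% power does not describe the baseline-adjusted contrast at T2 or at T3. That 98 also fits that contrast at r = 0.5 is specific to that correlation; over r = 0.3 to 0.7 the requirement runs from 118 to 68.

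The figure that matters now is power at N = 50 one-sided: about 57% to 79% for d = 0.5 over that range, below the stated 0.80 throughout. This assumes d = 0.5 at the visit tested, 1:1 allocation and a separate test at each visit. The implication of d = 1.0 at follow-up is conditional on T1 being one of the two occasions. Whether one-sided testing justifies the step from 98 to 50 is a separate question.

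**What to change.** In the Sample size section, replace the 2 x 2 repeated-measures ANOVA calculation with one for the baseline-adjusted arm difference at T2 and at T3. State:
- the standardised effect at that visit (d = 0.5 if that is what medium means);
- the assumed T1-T2 and T1-T3 correlations, shown as a range if no estimate is available;
- the resulting power at N = 50, one-sided: about 57%, 64% and 79% at r = 0.3, 0.5 and 0.7 for d = 0.5.

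If a joint test over T2 and T3 is intended instead, say so in the Goals and Data analysis sections and compute power for that test. If the original calculation is kept for the record, name its two occasions. Qualify the Discussion's statement on power to match. Dropping the non-sphericity input is cosmetic: at 1.0 with two occasions it changes nothing.

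The cost is rewording, with no new patients or data. The drawback is that the stated power becomes a range, below 80% under these assumptions.
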